### Sample size calculation

In a meta-analysis, Haff et al. [32] analyzed lottery trials targeted at various health behaviors, with a pooled success percentage of 57.5% in the lottery condition versus 22.6% in the control condition. A sample size calculation for detecting a 0.35 difference between proportions at *p* < .05 and a power (1-*β*) of 90%, indicated a sample size of 40 per condition. With an intra-class correlation coefficient of .05, based on a CRT by Van den Brand and colleagues [21] and an estimated cluster size *m* of 8, a design effect (1 + (*m*-1) x ICC) of 1.35 an effective sample size of 54 per condition was estimated. We aim to recruit a minimum of 64 participants per condition (meaning 8 clusters per condition), allowing 15% participant attrition over time. Based on the power calculation, we aim to assign 16 clusters to receive either a smoking-cessation training or a smoking-cessation training plus the smoke-free lottery.

### Retention

As a compensation for their participation in the study, participants are promised and given €30 at the end of the study, regardless of smoking status. To further prevent attrition and increase commitment to the study, we will hand all participants gadgets with the institute’s logo throughout the study (a water flask and mug) and send them a birthday and Christmas card on behalf of the study staff. Participants who do not respond to surveys or other measurements, receive a reminder text message and email.

## Intervention

This trial compares a control-arm to an intervention-arm. All participants get an anonymized trial-ID at the start of the trial.

### Control arm

As standard treatment, participants join the evidence-based group cessation training organized by SineFuma, which has been developed independent of this study and is based on Withdrawal-oriented Therapy [36] and Motivational Interviewing [37]. With certified trainers, SineFuma provides group training at work throughout the Netherlands. Among other topics, smokers learn to cope with cravings, social pressure and physical difficulties such as weight gain. The pre-existing training capitalizes peer support and informs smokers about the possibility to use medication to aid their cessation attempt. The group training has 7 meetings of 90 minutes, spread over 8 weeks and take place online or at the workplace. After 2 weeks of preparation and group forming, participants get a pause-week and jointly quit in the third meeting (in week 4). In the fourth meeting, participants should be smoke-free for 1 week. Participants are handed a personal CO-meter, that is linked to their smart-phone (see *measures*). Typically, groups can consist of a maximum of 16 participants, with an average of 10 [21]. After the outbreak of SARS-CoV-2, Sinefuma offers the training as e-health training online in identical form with a maximum group size of 8 participants.

### Intervention arm: smoke-free lottery

#### Weeks 1 to 13

Participants in the lottery arm receive the same treatment as the control arm in all aspects and additionally participate in lotteries. Prize sizes were chosen such that the weekly expenses per participant in proportion to the Dutch minimum wage were similar (0.6%) to a previous effective instance of this lottery [31]. We also mimic the lottery-deadline schedule in the best performing trial-arm to promote gym attendance in Van der Swaluw et al. [31]. Previous research shows that most relapse to smoking occurs in the early stages after quitting [38, 39], and that the added value of intervention is achieved mostly in the first 3 months [40, 41]. As a result, is has been proposed that cessation interventions should be ‘front-loaded’ [38]. Accordingly, we offer repeated weekly short-term lottery deadlines, immediately after the quit date. The lottery timeline is illustrated in Fig. 2.

**Fig. 2 Fig2:**
[figure not shown]
Timeline of the Lotteries

The first lottery deadline is 1 week after the joint quitting moment in the third training. From the fourth training, lottery participants can win €50 every week for 13 weeks. The winner is drawn out of all participants within a group using the trial-ID, regardless of their smoking status. Participants only receive their prize if they did not smoke that week, as confirmed by the CO-measurement. Participants are informed by text message and email about whether they have won the prize and whether they receive their prize.

Lottery winners who need to forfeit their prize because they smoked, will learn about their forgone prize. All other participants will be informed about whether the prize is awarded or not, but not to whom. Every week offers a new chance to win, irrespective of prior performance. If the winner is not eligible for the prize, the money is forfeited. If the winner has previously withdrawn from the study, the notary will draw a new winner.

To summarize, when participants are selected as a winner, they are informed about this. Next, if they smoked in the week before the draw, they do not get the prize. Other participants are then also informed that the winner did not get the prize because he or she smoked.

#### Weeks 14-26

After 26 weeks, all participants can win a family vacation voucher (worth €400). Again, the winners are drawn out of all participants within a group, regardless of their smoking status. The winner is always informed by text message and email. However, the winner only receives her prize if she was abstinent between weeks 14 and 26, as confirmed by the CO-measurement. If the winner is not eligible for the prize, a new winner is drawn until the prize can be awarded. All other participants will be informed that the prize is awarded or not, but not to whom.

The lotteries tested in this trial are distinct from conventional lotteries or quit and win contests because winning the lottery is not conditional on performance, but being able to claim the prize is. Participants are always in the drawing, irrespective of their performance. With this design, the lottery incentives take more the form of a commitment device [42], where people accept a presented deadline with the potential of finding out that they won a prize, but losing it because they did not stick to their own goal of not smoking.

As such, there are multiple design aspects that are meant to support people in achieving their own goal. First, the lotteries offer a vivid deadline with nearby consequences. This can help overcome an intrapersonal conflict between a farsighted *planner* that wants to quit smoking and shortsighted *doer* that wants to enjoy a cigarette. According to this model of self-control [43], people try to control their future myopic behavior to attain their long-term goals by restricting their future freedom of choice. Acceptance of a deadline with immediate feedback has been shown to achieve this [42, 44] and is therefore designed to obstruct the tendency to postpone the quitting attempt to enjoy a cigarette right now.

Second, people tend to overestimate their chances of winning a lottery [45]. Decision-making under risk is known to be influenced by emotional assessments of the outcomes and emotions at the time of the decision [46]. These emotions result in overweighting of small probabilities and especially for vivid outcomes [46]. As such, the potentially emotional effect of the lottery outcome is designed to increase the importance of the deadline.

Third, the lotteries -also dubbed *regret lotteries-* leverage the tendency to anticipate and avoid regret by only awarding prizes at the prespecified deadline to lottery winners who attained their health goals and always informing unsuccessful lottery winners what they would have won, had they attained their goal [47]. This way, participants know that they can compare the outcome of their decision to the counterfactual outcome, had they decided differently. If the alternative decision-option turned out better than the chosen option, people can feel regret [48]. More importantly, if people know in advance that they can compare outcomes, research shows that we anticipate regret and make regret-avoiding decisions [33]. In this study, we aim to link this emotion to people’s own goals. This way, anticipated regret of missing out on ones prize is meant to serve as a commitment device [47].

## Data collection

### Primary outcome

We use the Russell Standard (RS) to evaluate the outcome of the trial [49]. The primary outcome is the proportion of continuous abstinent participants 52 weeks after the initial quit date (t1 – t4). In the RS, abstinence is defined as a self-report of smoking not more than five cigarettes from the start of the abstinence period, supported by a negative biochemical validation at the final follow-up [49]. In our trial, this refers to smoking no more than five cigarettes between the quit day (t1) and the 52-week follow-up (t4). Smoking abstinence will be assessed via self-reports and is validated biochemically.

### Smoking abstinence self-reports

In both treatments, participants receive weekly text-messages from the start of the training until 13 weeks after the quit-date, to ask if they did or did not smoke that week. This 7-day point prevalence is determined by asking: have you smoked at all in the past 7 days? Participants can reply to the text message with a simple yes or no. The self-reports always take place 1 day before the CO-measurements. In the lottery arm, all measurements take place before the announcement of the lottery winner.

As part of the assessment of continuous abstinence at weeks 13, 26 and 52 after the quit date, we will ask: ‘Have you smoked at all since the quit date? A: No, never; B: 1–5 cigarettes; C: More than 5 cigarettes?’. Following the RS, answer A or B and a negative biochemical test are required for the participant to be classified as abstinent [49].

### Smoking abstinence carbon monoxide measurement

To biochemically verify smoking status, we use the validated non-invasive iCOquit Smokerlyzer® (Bedfont Scientific Ltd). The iCO measures CO-levels by requiring smokers to breath into the device. It is a strictly personal device that all participants receive by mail to their home address. Participants are asked to connect the device to their smartphone in order to use accompanied app. A tailored manual and instruction video was made for this trial and is sent to participants. Previous studies using smartphone CO-meters have shown personal mobile meters are suited to distinguish smokers from non-smokers and that usability is high [50, 51].

Participants receive a text message, asking them to perform and share the CO-measurement. After the measurement, results are presented in the app, that also allows participants to directly share their results with the trial staff via mail. Following the RS, we use a cut-off point of ≤9 ppm (p.p.m.) to determine smoking status. Measurements are weekly from the start of the training until 13 weeks after the quit date (of which 7 measurements are in the weeks of the training), and once at 26 and 52 weeks. Between weeks 14-26 there is one unannounced measurement. Participants know that it will ensue, but not in which week. If there is a difference between self-reported abstinence and biochemical validation or when participants do not respond, participants are assumed to have smoked. Following the RS, a failed biochemical test classifies a participant as smoking even when this is explained by the recent smoking of one to five cigarettes allowed throughout the follow-up period [49].

To summarize, when a participant reports not to have smoked more than five cigarettes between the quit-day and week 52, and this can be biochemically verified at week 52, they are considered not to have smoked. If previous measurements contradict this according to the criteria above, the participant is not considered continuously abstinent.

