An adjacent limitation is that unsuccessful participants might game the measurement by, for example, asking a non-smoker in their environment to breath into the device. In previous instances, CO-measurements were compared with urinary and salivary cotinine and only 4% of smokers reported falsely [68]. Likewise, even when there was a significant financial benefit in cheating, a trial with 604 participants found no differences between self-reports and CO-measurements [21]. We aim to prevent cheating by first asking to self-report smoking status and requiring the CO-measurement a day later and by stressing to participants that either smoking status (smoker or non-smoker) is acceptable to receive the study payment at the end of the study. At the main outcome point, there is also no financial incentive for cheating in either arm. By also using trusting and supporting langue throughout the trial (e.g., stating that relapse is never a personal failure), we aim to minimize this risk further.

A final limitation of the current study design is that it does not allow to disentangle the psychological mechanisms responsible for a potential effect. The lotteries host multiple components to leverage well-known influences on decision-making [26]. While we use surveys to explore perceptions and psychological constructs at work, trials with more than two treatment arms allow to vary more design characteristics to identify working mechanisms more precisely [69].

An important benefit of the current study design is the 6-month follow-up, after all lotteries have ended. A common pattern in the application of the current lotteries is that they especially support initial health behavior change, which declines after removal of the lottery deadlines [31, 32]. In contrast, research into smoking relapse curves suggest that not smoking might become ‘easier’ over time [41]. The present design allows us to explore which of the two patterns will be dominant.

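### The 52-week outcome can be overruled by earlier measurements under criteria that count non-response as smoking, while only the lottery arm has a prize tied to those earlier tests

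*Protocol article*

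**What the plan says.** Under Data collection, Primary outcome, the Russell Standard is adopted: a self-report of at most five cigarettes from the quit day, "supported by a negative biochemical validation at the final follow-up". In this trial that follow-up is week 52. Under Smoking abstinence self-reports, continuous abstinence is asked at weeks 13, 26 and 52 with three answers: none (A), one to five cigarettes (B), more than five (C).

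The section on the CO measurement repeats the week-52 rule: if the report holds and "this can be biochemically verified at week 52, they are considered not to have smoked". The next sentence restricts it: "If previous measurements contradict this according to the criteria above, the participant is not considered continuously abstinent". The criteria given earlier in that section include "when participants do not respond, participants are assumed to have smoked". They also state that a failed test counts as smoking even if the cause was one of the permitted cigarettes.

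Interim contact is frequent. CO is requested weekly to week 13, once unannounced in weeks 14-26, and at week 26. A weekly text to week 13 asks "have you smoked at all in the past 7 days", answered yes or no.

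In the lottery arm, the Weeks 1 to 13 section says: "Participants only receive their prize if they did not smoke that week, as confirmed by the CO-measurement". The €400 voucher at week 26 also needs CO confirmation. Both arms receive €30 at the end whatever their smoking status (Retention).

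**The concern.** The restriction does not say what counts as a contradiction. Because non-response is among the criteria, a literal reader would classify as a failure anyone who missed a single interim CO request or text, even with a clean report and a negative test at week 52. A weekly yes has a similar problem. The question asks about any smoking and carries no cigarette count, so it cannot be mapped to the five-cigarette allowance.

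This matters for the comparison because the interim requests are not neutral between arms. A lottery participant who is abstinent has a reason to submit that a control participant lacks. If the lotteries raise submission among abstainers, the strict rule raises measured 52-week abstinence without any change in smoking. The Strengths and limitations section offers the reassurance "At the main outcome point, there is also no financial incentive for cheating in either arm". That covers week 52 only, not the interim data that the restriction feeds into the week-52 classification. The week-13 and week-26 secondary outcomes are exposed more directly, since both fall on lottery deadlines.

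The Blinding section says that researchers are not blinded, so an unsettled endpoint rule could end up being settled with arm-level data in view.

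**Working it through.** **The plan's own figures.** The sample size reproduces: 57.5% against 22.6%, two-sided 5%, 90% power gives 40 per arm; 40 × (1 + 7 × 0.05) = 40 × 1.35 = 54; 54 / 0.85 = 63.5, so 64. There is no arithmetic error; the point concerns the outcome rule.

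**Number of interim CO requests after the quit date.** 13 weekly + 1 unannounced + 1 at week 26 = 15.

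**One participant under the two readings.** Answer A at week 52, CO of 9 ppm or less at week 52, one unanswered CO request in week 7. Under the Primary outcome section: abstinent. Under the literal restriction: smoking in week 7, hence not continuously abstinent.

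**Size under the literal reading.** Assumptions, none from the documents: true 52-week abstinence of 25% in both arms, no lottery effect on smoking, and abstainers answering 98% (lottery) or 95% (control) of CO requests.

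With independent responses, the share of true abstainers kept is r^15: 0.98^15 = 0.739 and 0.95^15 = 0.463. Measured abstinence is 0.25 × 0.739 = 18.5% against 0.25 × 0.463 = 11.6%.

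Non-response usually clusters within people. With a beta-binomial of mean r and within-person correlation ρ, the share kept is the product over i = 0 to 14 of (a + i)/(a + b + i), where a = r(1 − ρ)/ρ and b = (1 − r)(1 − ρ)/ρ. Gaps are taken before rounding.

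| ρ | kept, lottery v control | measured, lottery v control | spurious gap |
|---|---|---|---|
| 0 | 74% v 46% | 18.5% v 11.6% | 6.9 points |
| 0.1 | 83% v 63% | 20.8% v 15.7% | 5.1 points |
| 0.3 | 90% v 77% | 22.5% v 19.3% | 3.3 points |
| 0.5 | 94% v 85% | 23.4% v 21.1% | 2.3 points |

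For 99% against 97% response, the same formula gives gaps of 5.7, 3.9, 2.3 and 1.6 points.

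**False positives, independent responses only.** Simulating 2,000 trials per scenario (16 clusters of 8, intra-class correlation 0.05, random-intercept logistic model, 25% true abstinence) gave two-sided rejection of 6.4% with no difference in response, 11.8% at 99% v 97%, and 15.1% at 98% v 95%. A normal approximation with 64 / 1.35 = 47.4 effective participants per arm and 22.6% true abstinence gives about 10% and 14% for the last two. Within-person correlation would lower these.

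**Equal response in both arms.** There is no bias under the null, but abstainers are lost. On the plan's 57.5% v 22.6% with 47.4 effective per arm, power is 95% with no interim loss. At 98% response in both arms (independent), the rates become 0.575 × 0.739 = 42.5% and 0.226 × 0.739 = 16.7%, and power is 80%.

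**A narrower reading.** If non-response counts only at the formal assessments in weeks 13 and 26, then 95% against 90% response gives 0.25 × 0.95² = 22.6% against 0.25 × 0.90² = 20.3%, a gap of 2.3 points.

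**The case against.** A reader might infer that the protocol defines its primary outcome in two incompatible ways. It does not. The two summary sentences are a condition followed by a restriction, and the Strengths and limitations section shows that assessment at several time points is deliberate. This part of the defence stands: the rule is unresolved, not self-contradictory.

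It is also fair that the strict reading is not the only one. A missed test is arguably not a measurement, and a week assumed smoked need not mean more than five cigarettes. The weekly text is labelled a 7-day point prevalence item, whereas continuous abstinence has its own A/B/C question. But the document settles none of this. Smoking assumed from silence carries no cigarette count, and non-response sits among the criteria to which the restriction refers.

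A reader might further infer that the lottery arm is paid to submit tests and will certainly submit more. The documents do not support that. The weekly prize is a draw, about 1 in 8 at the planned cluster size, and requires a passed test. Reminders go to non-responders without distinction by arm (Retention). Differential response among abstainers is plausible but undocumented.

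Finally, treating non-response as smoking is a familiar conservative convention, and alternative missing-data analyses commonly sit in an analysis plan that is not shown. Their absence is not criticised here. The point is that a rule stated in this document reaches back over interim contacts.

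**Conclusion.** The concern holds as an unresolved rule capable of biasing the primary outcome. What the text establishes is that non-response counts as smoking without restriction to week 52, that earlier measurements can overrule the week-52 result on those criteria, and that all 15 interim CO requests fall where only the lottery arm has a CO-dependent prize. The plausible direction of bias is therefore towards the lottery.

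The size is not established by the documents. Under the literal reading, with 25% true abstinence and 98% v 95% response, the spurious gap is 6.9 points at most (independent responses) and 5.1 to 2.3 points with within-person correlation of 0.1 to 0.5. The simulated false-positive rates of 12% to 15% belong to the independent case and lie towards the upper end. If response is equal between arms, the cost is lost abstainers and power, not bias under the null. If the sponsor never intended interim non-response to count, the problem disappears once that is written down.

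**What to change.** State one primary definition: answer A or B at week 52 plus a week-52 CO reading of 9 ppm or less, with non-response at week 52 counted as smoking.

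Let interim data overrule this only on an observed contradiction: a report of more than five cigarettes, or an observed failed interim CO test under the protocol's existing failed-test rule. Interim non-response and a single weekly yes should not overrule it. Failed tests, including the unannounced one, must keep this role; allowing only answer C to overrule would discard objective evidence that the protocol says classifies a participant as smoking.

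Report the strict all-measurements version as a sensitivity analysis, and tabulate interim text and CO response by arm so that readers can judge whether submission differed.

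The change is wording only and should be made before arm-level outcome data are examined. Its cost is that some undocumented early relapse, in both arms, will rest on the week-52 self-report. Differential submission would still have a minor effect, since a failed test can be observed only if it is submitted; the response table would show how far that matters.

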### Secondary outcomes

Secondary smoking outcomes are continuous - and point prevalence abstinence at 13 weeks (t2) and 26 weeks (t3) and are measured as described above. Self-efficacy (SE) of smoking abstinence at t1-t4 and motivation to quit at baseline are measured to also study the determinants of SE and motivation to quit. We assess self-efficacy of smoking abstinence with the Dutch Smoking Abstinence Self-efficacy Questionnaire (SASEQ [52]). Motivation to quit is assessed with the Treatment Self-Regulation Questionnaire (TSRQ [53]). In the lottery arm, participants are asked about their attitudes towards the lotteries (e.g., to what extent they motivated participants to join the cessation training).

